| | Discuss the research design including but not limited to such issues as: probability of group assignment, potential for subject to be randomized to placebo group, use of control subjects, etc. | | --- | | |  | Twenty participants will complete procedures during treatment with placebo and study medication, in random order, using a within-subjects, double-blind, placebo-controlled design. There will be a two week period between each phase. The dose of doxazosin needed to alter the effects of cocaine is unknown and preclinical animal studies have not been conducted. Because of this, initially we will study the effects of a low dose of doxazosin (4mg daily) compared to placebo daily. Because this class of medication needs to be titrated upward due to the potential for hypotension, treatment will begin at 1mg and increased by 1mg increments every three days until 4mg is reached. Placebo will be dosed identically. Blood pressure (resting and orthostatic) will be assessed daily prior to dosing. Cocaine (0, 20, and 40mg) will be administered during treatment with 4mg doxazosin/placebo. On day 10, cocaine will be administered in ascending dose (20mg followed by 40mg) with the 0mg dose randomly interspersed to maintain the blind. Cardiovascular measures and subjective effects ratings will be assessed following cocaine administration. Participants will be monitored for stability on days 11 and 12 and discharged from the hospital on day 13. Discharge will only occur for subjects who have a supine BP of 100/65 mm Hg or higher, a seated blood pressure of 90/60 mm Hg or higher, and an orthostatic change upon standing of < 20 mm Hg systolic or < 10 mm Hg diastolic.  If 4mg doxazosin treatment is well tolerated but is not associated with alterations in the effects of cocaine, a second group of subjects will be studied using the same sample size. Treatment will begin at 1mg and increased by 1mg increments every three days until 8mg is reached. All study procedures will be identical as described above. Placebo will be dosed identically. | | --- | --- | | |

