| F2.  Procedure |
| |  | | --- | | |  | Screening Interested candidates will receive an explanation of the study purpose and requirements. If still interested, the candidates will be allowed to review, inquire about, and sign the study informed consent form. After providing informed consent, subjects proceed to the screening assessment phase of the study. A urine drug toxicology screen will be conducted for drugs of abuse. Some of this sample will be shared with Rice university to develop new tests for drug detection. A saliva sample will also be collected for this purpose. Candidates deemed eligible based on initial screening assessments will be administered a MINI by a trained mental health professional, to determine if there are any psychiatric conditions that might exclude the potential subject from participation. Blood will be collected for analysis of hematology and chemistry tests. These assessments must be completed within 14 days before intake. At the initial screening visit, restrictions on use of alcohol, drugs of abuse, and medications will be reviewed. All subjects will be required to sign a written statement that they will abstain from use of cocaine or other psychostimulants throughout the duration of their participation in the trial.  All applicants for study participation will receive counseling as part of their participation, and will be advised that treatment for drug abuse is indicated and available. Applicants not participating in the study will receive treatment referral information as appropriate. At completion of their participation, study subjects will again be advised that treatment is indicated and available, and will be given treatment referral information and assistance.  Participants will reside on the Research Commons for the duration of the study (about 28 days total). Participants must refrain from illicit and prescription drug use, and we will confirm compliance by urine testing and breath alcohol level testing. Passes and monitoring. Passes will not usually be allowed, and visitors will not be permitted. Participants’ belongings will be searched upon arrival.  The study schedule outlined below may change by a day or two due to scheduling issues and/or safety reasons. We will ask participants to complete the protocol twice (once being randomized to placebo and once being randomized to doxazosin, but this wont be required.   General Procedures: Participants will be studied while residing on the Research Commons. Cocaine administration sessions will be conducted at approximately the same time of day for a given participant. Experimental sessions will be several hours in duration and will be conducted in a quiet room with research and medical staff present. The room will contain an experimental station, equipped with a response console attached to a personal computer and video monitor. Heart rate, EKG, and blood pressure will be recorded throughout experimental sessions using an automatic monitoring system.   Smoking, caffeine, and food. Caffeine and food will be prohibited during and 90 min before study sessions excepting a 1 hour break for lunch.   Day 1-10: The study participants will be randomized to receive either doxazosin or placebo. Doxazosin treatment will begin at 1mg and will be increased by 1mg increments every three days until 4mg is reached. Placebo will be dosed identically. Prior to dosing doxazosin, and at 1 hour intervals after each dose from hours 2 through 6 after dosing, sitting and supine orthostatic blood pressure will be assessed.  Cardiovascular monitoring and discontinuation criteria For doxazosin to be administered, the following criteria must be met: 1. supine blood pressure above 100/65 mm Hg, 2. a seated blood pressure of above 90/60 mm Hg, 3. and an orthostatic change smaller than 20 mm Hg systolic or smaller than 10 mm Hg diastolic on standing. The dose will not be increased until the participant has met criteria for dosing and has received 3 doses at a given dose level.  a. Participants who do not meet the criteria above at any time during hours 2 through 6 after dosing will remain supine until the next BP assessment. b. Participants who do not meet the criteria above consistently from hours 2 through 6 after any dosing will not have their dose of doxazosin increased and will remain at the prior dosing level. c. Participants who do not meet the requirements for dosing increase (supine blood pressure > 100/65 mm Hg, a seated blood pressure of > 90/60 mm Hg, and an orthostatic change < 20 mm Hg systolic or <10 mm Hg diastolic on standing) for 6 days will have medication discontinued and they will be discontinued from the study.   Day 10: Cocaine 20mg, 40mg and matched placebo saline will be administered via IV push by the study physician on day 10, at hourly intervals, with the placebo dose randomly interspersed to maintain the blind. To ensure that subjects will not be at risk from cocaine, the resting pulse must be < 90 bpm and the blood pressure must be < 150 mmHg systolic and < 90 mmHg diastolic immediately prior to dosing. Heart rate and blood pressure measurements will be made prior to cocaine dosing and at 15-minute intervals thereafter until 30 minutes following the final dose. Visual-analogue scale ratings of “any cocaine effect”, “high”, “good effects”, “bad effects”, “like cocaine”, “desire cocaine”, “depressed”, “anxious”, “stimulated”, and “if you had access to cocaine right now, how likely would you be to use it?” will be collected at -15 min, 5 min, 10 min, 15 min, 20 min, 30 min, and 45 min after cocaine dosing. Participants will remain seated during experimental sessions except for brief visits to the lavatory.   All infusions will be administered in single-blind fashion. All experimental procedures will be conducted in a hospital room located in the GCRC. Infusions will be administered over 2 minutes by I.V. push. Vital signs must remain within values specified under Stopping Criteria for initiation of cocaine administration. An ACLS-certified physician will be present from 15 min before drug administration until at least 1 hour after cocaine administration. The physician will be available in house and on pager for at least 4 hours after drug administration. Heart rate will be measured using continuous ECG from 15 min prior to cocaine or placebo dosing until 2 hours after dosing. Blood pressure will be assessed at frequent intervals from 15 min prior to cocaine or placebo dosing until 2 hours after dosing.   Discharge Participants will be monitored for stability on days 11 and 12 and discharged from the hospital on day 13. Discharge will only occur for subjects who have a supine BP of 100/65 mm Hg or higher, a seated blood pressure of 90/60 mm Hg or higher, and an orthostatic change upon standing of < 20 mm Hg systolic or < 10 mm Hg diastolic. Prior to discharge subjects will have a physical examination and vital signs, and complete the Beck Depression Inventory-II. An assessment of adverse events will be completed.  Participants will have the choice of returning two weeks later to complete study procedures.   Stopping Rules Doxazosin Participants who do not meet the criteria listed above (supine blood pressure above 100/65 mm Hg, a seated blood pressure of greater than 90/60 mm Hg, and an orthostatic change smaller than 20 mm Hg systolic or smaller than 10 mm Hg diastolic on standing) at any time during hours 2 through 6 after dosing will remain supine until the next BP assessment. Participants who do not meet the criteria above consistently from hours 2 through 6 after any dosing will not have their dose of doxazosin increased and will remain at the prior dosing level. Participants showing syncope or dizziness that does not respond to sitting down will be discharged from the study.  Stopping Criteria for Further Participation Participants who do not meet the requirements for dosing increase for 6 days will have medication discontinued and they will be discontinued from the study.  Cocaine Cocaine will not be administered if there are clinically significant arrhythmias or if vital signs are outside of acceptable ranges, which are resting pulse below 90 bpm and blood pressure below 150mm Hg systolic and 90mm Hg diastolic. In addition, repeated doses of cocaine will not be administered (and the study physician will halt continued cocaine delivery) if there are behavioral manifestations of cocaine toxicity (agitation, psychosis, inability to cooperate with study procedures).   Stopping Criteria for Further Participation Subject participation will be terminated if any of the following events occur: 1. Systolic BP above 180 mm Hg sustained for 5 minutes or more; 2. Diastolic BP above 120 mm Hg sustained for 5 minutes or more; 3. Heart rate above (220 – age x 0.85) bpm sustained for 5 minutes or more. Note: if a single value exceeding the values above is detected, the readings will be repeated until it is determined whether or not the stopping criteria have been met.  Adverse event assessment and management. We will assess participants’ well-being daily. Spontaneously reported symptoms or complaints will be recorded and reported to the IRB and NIDA and the FDA if events are classified as serious. Specific guidelines have been developed to guide assessment and intervention in the event of cardiovascular toxicity, such as malignant hypertension, ventricular arrhythmia, chest pain, etc., and are in use for our other studies involving cocaine administration. These guidelines are intended to support rather than supersede clinical judgment. If needed, a code team responds. Participants needing to be transferred to a medical or ICU ward can be, though this has never been necessary.   Assessments see attached | | --- | --- | | |

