| | Distribution Plan: | | --- | | |  | Participants will be paid $40 in gift certificates for the completion of the screening. The payment schedule is shown below. $50 is the average compensation provided for each day, however, compensation increases over the course of the study to make up for the increasing difficulty participants may have abstaining from illicit cocaine use. If a participants leaves the study early, payment will be prorated.   Day 0 - $20 Day 1 - $20 Day 2 - $25 Day 3 - $30 Day 4 - $35 Day 5 - $40 Day 6 - $45 Day 7 - $50 Day 8 - $55 Day 9 - $60 Day 10 - $80 Day 11 - $100 Day 12 - $50 Day 13 - $50 total $660  In addition, participants will receive an extra $40 on Monday, which can be any study day, depending on the day of entry.This is to compensate for staying over the weekend. Payment on Day 11 is larger to serve as a study completion bonus. Subjects completing both phases will receive $1400 plus a $100 bonus. | | --- | --- | | |
|  |
| Section M:  Genetics |
| | How would you classify your genetic study? | | --- | | |  | DNA diagnostic study | | --- | --- | | |

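### The conditional 8 mg group cannot reach 8 mg before day 22, yet it inherits a calendar with cocaine on day 10 and discharge on day 13

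*Protocol*

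**What the plan says.** Section F1 (Design) studies 4 mg first. Dosing starts at 1 mg and rises by 1 mg every three days to 4 mg. The session is defined by dose, "Cocaine (0, 20, and 40mg) will be administered during treatment with 4mg doxazosin/placebo", and by day: "On day 10, cocaine will be administered in ascending dose (20mg followed by 40mg". Then: "Participants will be monitored for stability on days 11 and 12 and discharged from the hospital on day 13".

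If 4 mg is well tolerated but leaves the effects of cocaine unchanged, a second group of the same sample size starts at 1 mg and is "increased by 1mg increments every three days until 8mg is reached. All study procedures will be identical as described above".

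Section F2 (Procedure) bears on the timing in three ways:

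- Titration cannot be faster: "The dose will not be increased until the participant has met criteria for dosing and has received 3 doses at a given dose level".
- Flexibility is small: "The study schedule outlined below may change by a day or two due to scheduling issues and/or safety reasons".
- Residence is given once, for the whole study: "Participants will reside on the Research Commons for the duration of the study (about 28 days total".

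The day-by-day text in F2 describes titration to 4 mg only. The payment schedule in Section L lists days 0 to 13 and ends "Day 12 - $50 Day 13 - $50 total $660". The website advertisement in Section R describes a 28-day inpatient study. No calendar for the 8 mg group appears in the text available.

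**The concern.** The second group is given two instructions that cannot both be followed: titrate to 8 mg at three days per step, and keep procedures that place the cocaine session on day 10 and discharge on day 13.

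The group opens only after 4 mg has failed to alter the effects of cocaine. If staff keep to the written days, its participants receive cocaine at 4 mg at most. A further sample of the same size would then be exposed to intravenous cocaine, in a study that section E1 classes as above minimal risk with no prospect of direct benefit, without 8 mg being tested against cocaine. A null result could also be read as evidence about 8 mg. If staff instead complete the titration, the written session day, discharge day, length of stay and payment schedule all fail.

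**Working it through.** **Inputs.** Start 1 mg on day 1; step 1 mg every three days; targets 4 mg and 8 mg; session on day 10; discharge on day 13 (all F1, with the session and discharge days repeated in F2). At least three doses per level, and one or two days of flexibility (F2). Payment entries for days 0 to 13 (Section L).

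**Reproducing the protocol's own figure.** First day at dose D, with no holds = 1 + 3 × (D − 1).

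- D = 4: 1 + 3 × 3 = day 10. This is exactly the stated session day, so the titration rule is being read as intended.

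**Applying the same rule to the second group.**

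- D = 8: 1 + 3 × 7 = day 22.
- Gap to the written session: 22 − 10 = 12 days.
- Gap to the written discharge: 22 − 13 = 9 days.

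**Highest dose on the written days.** Dose on day d = min(8, 1 + floor((d − 1)/3)).

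| Day | Event in the written calendar | Highest scheduled dose |
|---|---|---|
| 10 | Cocaine session | 1 + floor(9/3) = 4 mg |
| 12 | Session moved by the full two days | 1 + floor(11/3) = 4 mg |
| 13 | Discharge | 1 + floor(12/3) = 5 mg |
| 22 | None | 1 + floor(21/3) = 8 mg |

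Blood-pressure holds can only delay this, by one day for each day held. Three hold days, for example, move the first 8 mg dose to day 25.

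**Length of stay.** The session-to-discharge interval is 13 − 10 = 3 days. Keeping it, discharge falls on 22 + 3 = day 25.

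- Written calendar: days 0 to 13 = 14 days per phase; 2 × 14 = 28, which matches the stated residence.
- 8 mg calendar: days 0 to 25 = 26 days per phase; 2 × 26 = 52.
- Excess: 26 − 14 = 12 days per phase; 52 − 28 = 24 days for a participant who completes both phases (the second is optional).

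**Payment.** The 14 daily entries sum to $660. Adding the $40 Monday payment gives $700 per phase, and 700/14 = $50 per day, the stated average. Two phases give $1,400; with the $100 bonus and $40 for screening this is $1,540, the total in Section L. That total therefore contains nothing for the extra days. As an illustration only, if the $50 average continued: 12 × 50 = $600 more per phase, or 24 × 50 = $1,200 for both.

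**The case against.** The strongest reply is that carrying over identical procedures was never meant to carry over the day numbers. Read literally, the sentence would also carry over 4 mg as the dose at the session, which defeats the purpose of the group. Since day 10 is simply the first day at 4 mg, the natural reading is that the session happens at the target dose. Dosing is daily with blood-pressure checks, so staff would notice the mismatch before giving cocaine. The stay, payment and advertising text fit the group now being recruited and could be updated if the second group opens. An attachment or the consent form, neither available here, might hold an 8 mg schedule.

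Much of this is fair. The milder reading is plausible, which makes an actual retest of 4 mg a risk and not a certainty. The second group is conditional, and nothing about the first changes. The 52-day figure counts day 0 and the discharge day; counting from day 1 gives 2 × 25 = 50 against 2 × 13 = 26, with the same 24-day excess. The dollar figures are rough, because the $50 average includes an enlarged completion payment and one Monday payment, and a longer stay would contain more Mondays.

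The reply does not rescue the text. The protocol nowhere says that the session moves with the dose, and the only flexibility it grants is one or two days against a 12-day gap. On the milder reading the written session and discharge days are wrong for this group, and the stay and payment schedule cannot hold. A schedule in an attachment would itself conflict with the body of the protocol.

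**Conclusion.** The concern holds and should be fixed before the second group opens. Under the stated titration the first possible 8 mg day is day 22, 12 days after the written session, and the highest dose within the permitted flexibility is 4 mg. Following the calendar means 8 mg is not tested with cocaine; following the titration means 26 days per phase instead of 14, with no payment entry for the additional 12.

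This is a conflict between stated rules on dosing, session and discharge days. These are protocol content, not detail that could be left to an analysis plan. Day 22 assumes dosing from day 1 with no holds, so it is the earliest case. Day 25 and the 26-day stay also assume the same three-day interval from session to discharge. The payment illustration assumes the $50 daily average continues.

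**What to change.** Replace the sentence in F1 that carries all procedures over unchanged with a calendar for the second group, and repeat it in F2:

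- Tie the cocaine session to reaching 8 mg: day 22 at the earliest, later by each day a dose is held. State 8 mg, not 4 mg, as the dose at that session.
- Place monitoring on the two days after the session and discharge about day 25, if the present spacing is kept.
- Restate the length of stay (about 26 days per phase, about 52 for those completing both), the Section L payment schedule and the 28-day recruitment text for that group.

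If the sponsor prefers to keep the day-10 session and day-13 discharge, label the group with the dose it actually reaches. Which option to take is the sponsor's clinical decision.

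The cost is a protocol amendment for a conditional group and, only if 8 mg is to be tested, the longer stay and payment that the protocol's own titration already implies. Any consent change depends on a form not available here. The first group bears no cost.
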